#### 2.1.2 Secondary objectives.

To define the prevalence of neurocognitive deficits in cancer survivors in our population.To analyze psychological and emotional self-perception and parent perception after controlled intervention with video games (Behavioral Assessment System for Children and Adolescents, third edition, BASC-3).To assess the feasibility of implementing a new intervention methodology through technological games.

### Trial population

A sample of 56 patients will be recruited in the study from among the patients of the Department of Pediatric Hemato-Oncology of an academic hospital in Spain between 8 and 17 years of age who have completed cancer treatment 1 to 8 years before enrolment. All patients provided written informed consent before any study procedure. The patients will be randomized in a 1:1 ratio to either the treatment group or the waiting group, after stratification for age, one group from 8 to 12 years, and the other group from 13 to 17 years of age.

There will also be a control group of healthy patients (who have not suffered an oncological disease) in which structural and functional MRI will be performed with the same protocol as in the waiting and treatment groups. This group will establish a standard of comparison for neuroimaging tests of patients in the study. It is intended to recruit 20 patients in this group, 10 patients aged 8 to 12 years, and 10 patients aged 13 to 17 years. Patients will be selected from among siblings or other families of the intervention/waiting group.

Recruitment will be made from the patients of the Department of Pediatric Hemato-Oncology follow-up visits via telephone calls and face-to-face appointments if required to explain the study to both parents and participants themselves.

#### 2.1.3 Selection criteria for the treatment/waiting group.

**Inclusion criteria**

Patients aged between 8 and 17 years at the time of recruitment.Have completed treatment between one and eight years prior to enrollment.Have had one of the following diagnoses:CNS cancer (posterior fossa tumors and supratentorial gliomas < 1 cm affecting the associative areas).Hematologic malignancies (leukemia or lymphoma).Extracranial solid tumors.Nonmalignant hematological diseases and indications for allogeneic hematopoietic progenitor transplantation.Having received at least one of the following treatments:CNS surgery.CNS radiotherapy.Intrathecal and intraventricular chemotherapy.Neurotoxic systemic chemotherapy.Hematopoietic stem cell transplantation.Informed consent was obtained from the patient’s parent/guardian.

**Exclusion criteria**

Active oncologic disease or relapse.Prior neurological or psychiatric pathology that may preclude trial or treatment evaluations:Psychological or neurocognitive illness or sequelae that preclude neuropsychological assessment or are expected to significantly artifact MRI results (e.g., significant decrease in visual acuity, CNS surgical scar that artifacts imaging results, severe cognitive delay that precludes testing).Psychological or neurocognitive illnesses or sequelae that prevent or contraindicate the use of video games (epilepsy that prevents the use of screens, significant decrease in visual acuity, etc.).Mild or self-limiting neurological or psychiatric pathology that does not interfere with trial diagnosis and treatment (headache, epilepsy in remission with effective treatment, mild cognitive delay) will be allowed.Current or recent (less than one year) use of other cognitive stimulation or brain training that may interfere with the study results.Refusal to abstain from the use of the study treatment games in case of being assigned to Group B (waiting group).Medical treatment that may significantly interfere with neuropsychological, imaging or biomarker assessments.

#### 2.1.4 Selection criteria for the control group of healthy patients.

**Inclusion criteria**

Patients aged between 8 and 17 years at the time of recruitment.Informed consent was obtained from the patient’s parent/guardian.

**Exclusion criteria**

History of oncological disease and/or treatment with neurotoxic potential.Psychological or neurocognitive illness or sequelae that preclude neuropsychological assessment or are expected to significantly artifact MRI results (e.g., significant decrease in visual acuity, CNS surgical scar that artifacts imaging results, severe cognitive delay that precludes testing).Current or recent (less than one year) use of other cognitive stimulation or brain training that may interfere with the study results.

#### 2.1.5 Study withdrawal.

Death.Relapse of the underlying disease or other oncological pathologies or pathologies requiring intensive medical treatment.Decision of the patient or their parent/guardian.Concomitant use of another cognitive training platform.Use of experimental group games among patients in group B (control group).Medical indication for treatment that interferes with trial measures. Mildly interfering treatments (e.g., methylphenidate-derived drugs) will be allowed, provided that the date of treatment initiation, date of dose modification, and dosages are documented.

### Variables and instruments

The variables measured in this project, the instruments used and the informants who will complete each measure are detailed below:

Sociodemographic (sex, age, educational level) and clinical variables (weight and height, blood pressure, heart rate, physical examination, and neurological examination). This data will be collected with an initial survey created *ad hoc* for the present study.Ecological Executive Functioning. The BRIEF-2 questionnaire [15] will be used. This questionnaire will be completed by the patient’s parents or legal guardians.Emotional and behavioral problems. The BASC-3 [16] will be administered, including both parent-reported and self-reported versions. This questionnaire assesses the personal and interpersonal/social domains of each patient, covering areas such as adaptive skills, resiliency, externalizing and internalizing problems, school problems, and relationships with parents and peers.Cognitive processing speed. The SDMT [17] will be administered to patients, in its oral form, to assess their processing speed of information.Visual sustained attention/vigilance. The CPT 3 [18], will be administered to the patients. This test computes several scores, as follows: Detectability, Omissions, Commissions, Perseverations, Hit Reaction Time (HRT), HRT Standard Deviation, Variability, HRT Block Change and HRT Inter-Stimulus Interval Change.Immediate and delayed verbal memory. A Spanish test based on the California Verbal Learning Test will be used. Specifically, the TAVECI [19] will be administered to patients aged 8–16 years, and the TAVEC version [20] will be applied to patients aged 16–18 years. This test allows for the calculation of a wide range of scores, and in this study, the following scores will be used: Immediate Recall, Short Delay Free Recall, Short Delay Cued Recall, Long Delay Free Recall, Long Delay Cued Recall, Long Delay Recognition, Semantic clustering strategies, Serial clustering strategies, False positives, and Discriminability.Semantic memory. The WISC-V [21] will be administered to patients up to the age of 16.11 years, and the adult version, fourth edition (WAIS-IV) [22], will be administered to patients up to 18 years of age.Verbal working memory and cognitive flexibility. The Digit Span subtest of the WISC-V [21] or WAIS-IV version [22] will be used. Three neurocognitive domain-specific scores will be considered (Forward, Backward, and Sequencing subscales), as well as the global score (Digit Span), as a measure of cognitive flexibility [21].Verbal fluency. The Verbal Fluency Test (TFV) [23] will be administered to patients, calculating the following eight scores: Phonological fluency, Semantic fluency, Excluded-letter fluency, Total Fluency Index, Errors in phonological fluency, Errors in semantic fluency, Errors in excluded-letter fluency and Total errors.Cognitive interference inhibition. The STROOP test [24] will be applied to patients and the following four scores will be computed: the Word reading, the Color naming, the Color-word and Resistance to Interference.Visuo-constructive organizational ability and immediate and delayed visual memory. The Rey Complex Figure Test (RCFT) [25] will be applied to patients, generating the following four scores: a copy score (accuracy regarding visual–spatial constructional ability), time required to copy the figure, and two delayed recall scores (at 3 and 30 min).Non-verbal Intelligence. Both forms (A and B) of the TONI-4 [26] will be administered to the patients.Structural image: volume of white matter, gray matter, total intracranial volume, volume of cerebral lobes, and different subcortical structures. Voxel-based morphometry (VBM).Diffusion Imaging: diffusion maps (fractional anisotropy, mean diffusivity, etc.) and structural integrity.Functional imaging: Task-based fMRI: functional differences related to a working memory task; Resting State fMRI: analysis of functional connectivity (Seed Based Analysis and Independent Component Analysis).Study of lymphocyte populations by parametric flow cytometry: T lymphocytes, B lymphocytes, NK lymphocytes, and NK T lymphocytes.Study of inflammatory cytokines: IL-2, IL-4, IL-6, TNF alpha, IFN gamma, IL-10, IL-17a, IL-1R antagonist.

All neuropsychological tests and patient questionnaires will be administered by clinical neuropsychologists from the Department of Psychiatry, Clinical Psychology and Mental Health of the hospital. Neuroimaging tests will be performed by trained technicians, and the data will be analyzed by researchers with expertise in structural and functional neuroimaging.

The selected inflammatory and immune biomarkers were chosen based on prior evidence of their involvement in cancer-related cognitive impairment (CRCI) and neuroinflammation. Pro-inflammatory cytokines such as IL-6 and TNF-α have been associated with cognitive dysfunction in both pediatric and adult oncology populations. IL-10 and IL-1 receptor antagonists (IL-1RA) represent anti-inflammatory responses that may indicate compensatory immune regulation. The inclusion of Th1 (e.g., IL-2, IFN-γ), Th2 (e.g., IL-4, IL-10), and Th17 (e.g., IL-17a) cytokines provides a broader immunological context to explore the potential links between immune activation profiles and cognitive or neural changes in survivors.

### Interventions

#### 2.1.6 Experimental intervention.

The patient will receive treatment for a period of 12 weeks, in which they will commit to using the video games of the intervention with the following pattern:

“Brain-training game” (Sincrolab^®^): sessions of 7-12 minutes with a frequency of 4 days a week.“Exer-gaming” (Just Dance^®^ in the 8-12 year-old group and Ring Fit Adventure^®^ in the 13-17 year-old group): sessions of 15-20 minutes 2 days a week.“Skill-training games” (Minecraft Education^®^): sessions of 15-20 minutes 2 days a week.

Adherence to the training program will be monitored using the game’s own game-tracking system (Sincrolab and Minecraft Education). In the case of games without their own system (the two exer-gaming games), video calls will be made with the participant during game time, in addition to weekly phone calls, to ensure the correct follow-up of the program, resolve doubts, and provide technical support.

#### 2.1.7 Waiting group.

These patients will not receive the experimental training program for the duration of the trial and will only be evaluated as the intervention group. Nonetheless, every patient will be offered the training program after completing the study.

### Informed consent procedure

Informed consent will be obtained before any specific study procedure is performed. Eligible subjects and their family members or legal representative(s) will be informed about the objectives and procedures before the start of the study. Minors older than 12 years of age, in addition to the informed consent signed by their legal representative, must give their consent.

### Schedule of trial procedures

Table 1 summarizes the procedures that will be performed for each patient.

**Table 1 pone.0314118.t001:** Schedule of Trial Procedures.

Trial period	Screening	T0	Treatment/waiting period						T + 3	T + 6
Weeks	−4	−4 to −1	1	3	5	7	9	11	13 to 17	25 to 29
Informed consent	X									
Inclusion and exclusion criteria	X									
Demographic data and medical history	X									
Concomitant medication	X					X			X	
Incidents during treatment	X					X			X	
Physical examination and vital signs	X								X	
Biomarkers		X							X	X
Neuropsychological evaluation		X							X	X
Neuroimaging evaluation		X							X	X
Habits and psychosocial survey		X								X
Adherence evaluation*			X	X	X	X	X	X		

*Only in the intervention group. Study investigators will review the activity recorded by compatible gaming platforms, and will contact the patient and family to verify adherence to treatment.

### Statistical methods

The data will be processed primarily using the statistical software IBM SPSS Statistics 30.0, among others, and the following analyses will be performed:

Initially, descriptive analyses will be performed on all the variables to detect any potential errors or outliers in the dataset. Zero-order correlation analyses will then be computed to determine the strength of association between the variables, and partial correlation analyses will be conducted to assess the association while excluding the influence of confounding variables.

The main statistical analysis will consist of a mixed Analysis of Covariance (ANCOVA) to evaluate between-group effects (intervention vs. waiting list), within-group effects over time (T0, T + 3, and T + 6), and their interactions, controlling for relevant covariates. These covariates will include age, sex, baseline cognitive performance, cancer diagnosis, and treatment modality (e.g., CNS radiation, neurotoxic chemotherapy). *P*-value adjustments will be performed for multiple comparisons. Assumptions of normality, homogeneity of variances, and sphericity will be examined and addressed as needed. Additional analyses will include latent growth models to examine cognitive trajectories, and multiple linear regression models to determine the relative contribution of predictor variables on outcome measures, as previously described [27].

The diagnostic group (CNS vs. non-CNS tumors) will be included as a covariate in the main analyses, and exploratory subgroup comparisons between CNS and non-CNS survivors will be conducted to assess the potential differences in cognitive, neuroimaging, and biomarker outcomes.

All statistical analyses will be complemented with appropriate effect size indices for each statistical test (e.g., *f*, omega square, and *R*^*2*^ indices) [28]. Additionally, the Reliable Change Index (RCI) will be computed to determine the real change in each individual score between measurements over time [29].

The original power analysis was performed using GPower 3.1.9.4, assuming a repeated-measures ANCOVA (2 × 3 design) with a statistical power of 0.95, α = 0.05, and a moderate effect size (f = 0.25), resulting in a minimum required sample size of 36 participants. However, because GPower does not account for intra-subject correlation (ICC), this estimation corresponds to a fixed-effects model. As the analysis will use a mixed model with repeated measures, we acknowledge that the ICC could affect power. To increase transparency, we have considered ICC values between 0.3 and 0.6, which suggest that between 42 and 48 participants may be needed to maintain the same level of power. This is feasible within our recruitment plan.

Missing data will be handled using multiple imputation under the missing-at-random (MAR) assumption. Sensitivity analyses will compare the imputed results with complete-case analyses, and other techniques, such as pattern-mixture models, may be used if appropriate.Randomization will be performed automatically using the REDCap platform and stratified by age group. Once a patient has been assigned, the study investigators will inform them and their families via telephone calls.

Investigators responsible for the clinical follow-up will not be blinded. However, those conducting neuropsychological and neuroimaging assessments will be blinded to group allocation to minimize bias in the outcome evaluation.

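### The sample sizes of 36 and 42–48 do not follow from the stated inputs, the ICC works in the opposite direction, and 0.95 power is not met at ICC 0.3

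*Protocol article*

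**What the plan says.** The power paragraph under Statistical methods in the protocol article describes its calculation as "assuming a repeated-measures ANCOVA (2 × 3 design) with a statistical power of 0.95, α = 0.05, and a moderate effect size (f = 0.25"). The total it reports from these inputs is worded "resulting in a minimum required sample size of 36 participants". On the correlation, the text says that "because GPower does not account for intra-subject correlation (ICC), this estimation corresponds to a fixed-effects model". To allow for it, the authors report that "we have considered ICC values between 0.3 and 0.6". The conclusion they draw from this range reads "which suggest that between 42 and 48 participants may be needed to maintain the same level of power", and they call that number feasible for their recruitment.

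The same section sets three assessments (T0, T+3, T+6) and a mixed ANCOVA with between-group, within-group and interaction effects. The Trial population section plans 56 patients randomized 1:1, but does not derive that number. The article states no correlation for the figure of 36 and no dropout rate.

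**The concern.** Three statements in this paragraph conflict.

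- **The 36.** A repeated-measures test of a time effect or a group-by-time effect cannot be powered without a value for the correlation between visits, whether entered or left at a default. If 36 truly ignored correlation, it should match the answer at zero correlation.
- **The direction.** For group-by-time, stronger within-subject correlation removes more between-subject variance from the error term, so the required N falls as the ICC rises. The paragraph treats the ICC as something that pushes N up from 36.
- **The range.** The article says 42–48 covers ICC 0.3 to 0.6 at the same power. The requirement varies far more than that over this range.

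This paragraph is the only justification of the trial's size. If it is wrong, a null result could be read as coming from a trial with 95% power when the stated inputs do not support that.

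**Working it through.** **Inputs (all from the article).** Groups k = 2, visits m = 3, f = 0.25, α = 0.05, target power 0.95, ICC (ρ) 0.3 to 0.6, 1:1 allocation, 56 planned. Assumed: compound symmetry (so sphericity holds), no attrition and no variance reduction from covariates.

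**Formula, group-by-time interaction.** Noncentral F with

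- λ = f² · N · m / (1 − ρ)
- df1 = (k − 1)(m − 1) = 2
- df2 = (N − k)(m − 1) = 2(N − 2)

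**Step 1: reproduce the 36.**

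- At ρ = 0: λ = 0.0625 × 36 × 3 / 1 = 6.75, df2 = 68, critical F = 3.13, power 0.62. Power 0.95 needs N = 84 (λ = 15.75).
- At ρ = 0.6: λ = 6.75 / 0.4 = 16.875, power 0.958. With N = 34 it is 0.947, so 36 is the smallest even N.

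With three visits, α = 0.05 and power 0.95, 36 therefore arises at ρ = 0.6. It also arises from settings the article does not state: four visits at ρ = 0.5, power 0.90 at ρ = 0.5, or α = 0.10 at ρ = 0.5. A fixed-effects ANCOVA without repeated measures needs about 210 to 251. None of these is a correlation-free 36.

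**Step 2: required N over the plan's ICC range.**

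| ICC | N for power 0.95 |
|---|---|
| 0 | 84 |
| 0.3 | 60 |
| 0.4 | 52 |
| 0.5 | 44 |
| 0.6 | 36 |

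The range is 60 down to 36. A requirement of 42 to 48 corresponds only to ICC of about 0.44 to 0.52.

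**Step 3: try the group main effect.** Here λ = f² · N · m / (1 + (m − 1)ρ), df1 = 1, df2 = N − 2. N does rise with ICC, but it is 114 at ρ = 0.3 and 156 at ρ = 0.6. The within-subject time effect gives the same N as the interaction. Other numbers of groups or visits, lower power, larger α, non-sphericity and loss of covariate degrees of freedom were also tried. None gives 36 followed by 42–48 over ICC 0.3–0.6.

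**Step 4: power of the sizes named.**

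| N | ICC 0.3 | ICC 0.4 | ICC 0.5 | ICC 0.6 |
|---|---|---|---|---|
| 36 | 0.781 | 0.844 | 0.906 | 0.958 |
| 42 | 0.847 | 0.900 | 0.946 | 0.980 |
| 48 | 0.895 | 0.937 | 0.970 | 0.991 |
| 56 | 0.938 | 0.967 | 0.987 | 0.997 |

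Example at ICC 0.3, N = 48: λ = 0.0625 × 48 × 3 / 0.7 = 12.86, df2 = 92, critical F = 3.10, power 0.895.

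**Step 5: simulation check** (4,000 runs per cell). At ICC 0.3: N = 36 gives 0.788, 42 gives 0.851, 48 gives 0.896 and 56 gives 0.947. These agree with the formula to within about 0.01.

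**The case against.** The strongest reply is that the trial plans 56 patients, not 36, 42 or 48. At the worst ICC in the stated range, 56 gives 0.938, which is 1.2 points below target, and by the same formula 56 reaches 0.95 at ICC 0.34. So the planned size is adequate, or nearly so, over almost the whole range. This stands, and it limits the practical shortfall. It does not rescue the statement that 42–48 keep power at 0.95, which fails by 5 to 10 points at ICC 0.3. The 0.938 also needs all 56 to be evaluable: with 50 it is 0.908.

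Second, the origin of 36 cannot be settled, since several unstated settings give it. This also stands. What can be said is that, of the ICC values in the plan, only the top one gives 36 with the stated inputs, and that the text's denial that correlation was involved cannot be right.

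Third, the article does not name the powered effect, so choosing group-by-time is an inference. It is the natural reading for a comparison of change between arms, and the group main effect fits much worse.

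Fourth, the recomputed figures rest on sphericity and ignore covariates. With ε = 0.75, N becomes 74, 64, 54 and 44 at ICC 0.3, 0.4, 0.5 and 0.6. Covariate adjustment would work the other way: an assumed 5% cut in residual variance, with 6 degrees of freedom lost, lifts 56 at ICC 0.3 to 0.949. These assumptions belong beside the replacement figures. They do not make the printed ones reproducible.

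**Conclusion.** The concern holds. The 36 is not a correlation-free figure: the stated inputs need 84 at zero correlation and reach 36 at ICC 0.6. The 42–48 does not match ICC 0.3 to 0.6, for which the group-by-time test needs 60 down to 36. The stated effect of the ICC has the wrong direction for that test.

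At ICC 0.3 the requirement of 60 is 25% above the stated upper figure (60 / 48 = 1.25) and 4 above the planned 56. Power there is 0.85 to 0.90 for 42 to 48, which puts the type II error at two to three times the 5% claimed. For 56 fully evaluable patients the deficit is small (0.938 against 0.95), and at ICC 0.4 or above the target is met. The recomputation assumes that group-by-time is the powered effect, that sphericity holds, and that neither attrition nor covariate gain applies.

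**What to change.** Replace the power paragraph with one that can be reproduced:

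- Name the powered effect (group-by-time interaction, if the sponsor confirms it), with 2 groups, 3 visits, f = 0.25, α = 0.05 and power 0.95, and state that sphericity is assumed and covariate gain ignored.
- Give the required N as 60, 52, 44 and 36 for ICC 0.3, 0.4, 0.5 and 0.6.
- Delete the statements that the correlation is not accounted for and that 36 is a fixed-effects figure.
- State the power of the planned 56 (0.94, 0.97, 0.99, 0.997 at those ICC values) and of 48 evaluable as an attrition case (0.90, 0.94, 0.97, 0.99).

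The cost is one rewritten paragraph and a slightly less favourable power statement at low ICC. Recruitment, endpoints and analysis do not change.
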